### Patient evaluation and quality indicators

Each patient was followed for 12 months. Overnight fasting levels of HbA_1c_, glycaemia, total cholesterol, HDL- and LDL-cholesterol and TG were determined at each visit. Blood samples were sent to a central laboratory (Bio Analytical Research Corporation [BARC], Ghent, Belgium) for analysis. HbA_1c _was measured using ion-exchange high performance liquid chromatography (HPLC) (Adams A_1c _HA8160, Arkray, Kyoto, Japan). LDL-cholesterol data from evaluable patients was estimated using Friedewald's formula, which uses total cholesterol, HDL-cholesterol and fasting TG when the latter are < 400 mg/dL. Urine was analysed for microalbuminuria at Visits 1 and 4 using an immunoturbidimetric assay (Modular P analyser, Roche Diagnostics, Mannheim, Germany).

Casual (resting) BP, waist circumference, weight and height were measured by the physician at each visit. BP was measured using a manometer with an appropriately sized cuff with the patient in the sitting position for at least 5 minutes prior to the reading. A mean value was determined from three successive readings and recorded. Waist circumference was measured using a measuring tape placed around the patient's abdomen at the level of the iliac crest and at the end of normal expiration. Patients wore light clothing and no shoes during weight measurement - values were rounded up to the nearest kg from 0.5 kg. Patients wore no shoes during height measurement - values were rounded up to the nearest cm from 0.5 cm.

A history of proteinuria at baseline was established from proteinuria levels in the patient's medical records and computed in the electronic Case Report Form (eCRF). Smoking status was also recorded in the eCRF as smoker/ex-smoker/non-smoker, together with the number of cigarettes, cigars or pipes that the patient was smoking, or had smoked per day. In addition, records were kept of whether or not a needs assessment for low-dose aspirin therapy (as an antiplatelet agent) had been performed during the 12 months of the study, as at the time the protocol was written, this was a recommended parameter to be taken into consideration for patients with T2DM [16]. Optional assessment by the treating physician at each visit of the degree of physical activity could be carried out using a step counter. A four-point verbal rating scale (VRS) was used to assess total physical activity with the following criteria; no weekly activity; only limited physical activity during most weeks; intense physical activity (activity that gives rise to shortness of breath, tachycardia and sweating) during at least 20 minutes, once to twice a week; intense physical activity (activity that gives rise to shortness of breath, tachycardia and sweating) during at least 20 minutes, ≥3 times a week.

Critical quality indicators used for benchmarking were HbA_1c_, LDL-cholesterol and SBP. Secondary quality indicators, not used for benchmarking, were blood glucose, TG, total and HDL-cholesterol, diastolic blood pressure (DBP), BMI, waist circumference and smoking status. Whether or not dietary advice had been given (and by whom), and whether screening for retinopathy and foot examination had been performed during the 12 months of the investigation, were also recorded and analysed as secondary quality indicators but were not part of the benchmarking feedback.

### Target setting for benchmarking

The targets set for the critical quality indicators (HbA_1c_, LDL-cholesterol and SBP) used for benchmarking were based on international guidelines [16-18], and, when deemed necessary, adapted by the study steering committee in order to be consensual to the participating countries (Table 1).

**Table 1 T1:** OPTIMISE Study: Targets set for benchmarking

	SBP (mmHg)	LDL-cholesterol (mg/dL)	**HbA**_**1c**_ (%)
All countries	< 130*	< 100^†^	< 7.0
Belgium		< 80^†^	

*Patients with proteinuria < 125 mmHg

^†^Patients with existing coronary heart disease < 70 mg/dL

For physicians in the benchmarking group, benchmarked feedback was given to each practice for both the pooled patient population at that practice, and at an individual patient level (Figure 3). A bi-modal response was given (good, too high) for each of the critical quality indicators, signifying whether or not the patient/clinic had achieved targets. In Belgium, the National Steering Committee opted for a tri-modal response: HbA_1c _≤7.0% = excellent, 7.1-7.5% = borderline, > 7.5% = too high; SBP < 130 mmHg = excellent, 130-139 mmHg = borderline, ≥140 mmHg = too high; LDL-cholesterol < 80 mg/dL = excellent, 80-99 mg/dL = good, ≥100 mg/dL = too high (< 70 mg/dL = excellent in secondary prevention).

**Figure 3 F3:**
[figure not shown]
**Example of benchmarking in OPTIMISE**. Reproduced with permission from Whathealth.eu. SBP, systolic blood pressure.

### Statistical considerations

In this study, all patients treated by an investigator received the same type of follow up (either benchmarking or standard). Since each investigator may have a particular approach for monitoring, counselling and treating their patients with T2DM, it was expected that this might result in an investigator or cluster effect. The extent of this effect is reflected by the Intracluster Correlation Coefficient (ICC) which, according to the literature, varies for BP between 0.05 and 0.10, indicating a clustering influence of 5-10% [19-21]. Of the three critical quality indicators used for benchmarking, SBP was expected to be the least well controlled at baseline. Therefore, for the purposes of study sample size calculations, it was considered most important to be able to demonstrate significance in the improvement in proportion of patients achieving the pre-set targets for SBP.

For example in the Best study [22], blood pressure was controlled in only 12.3% of patients at baseline; however, the proportion of patients with their blood pressure under control increased by 68.3% after 6 months of more intensive follow up. Due to the stricter target (130/80 mmHg in the OPTIMISE study compared with 140/90 mmHg) and the longer duration of this study, an improvement of 88.7% could be expected in the proportion of patients reaching blood pressure targets in both groups, from 12.3% to 23.2% in the control group and the benchmarking group under the null hypothesis (the null hypothesis is that the percentages in both groups are equal). There are relatively few previous studies reporting the level of improvement seen when benchmarking was used. However, review of those available [23-27] suggest that the level of improvement that might be expected ranges from 15-51%. Based on these findings it was estimated that the use of benchmarking in OPTIMISE could further improve the level of blood pressure control by 32%, i.e from 23.2 to 30.6% (the alternative hypothesis is that the percentage in the benchmarking group is larger than in the control group). With 3000 evaluable patients in the benchmarking group (300 clusters of 10 patients) and 1000 patients in the control group (100 clusters of 10 patients), a two-sided Z test (unpooled) would give 91%, 86% and 80% power to detect a 74% difference between the proportion of patients on target for SBP for an ICC of 0.05, 0.07 and 0.10 (between 5 and 10%).

As some centres included up to 20 patients, sample size calculations were adapted. With 3000 evaluable patients in the benchmarking group (200 clusters of 15 patients) and 1000 patients in the control group (67 clusters of 15 patients), there would be 96%, 93% and 88% power to detect a 74% difference between the proportion of patients on target for SBP for an ICC of 0.05, 0.07 and 0.10, respectively, p = 0.05. With 3000 evaluable patients in the benchmarking group (150 clusters of 20 patients) and 1000 patients in the control group (50 clusters of 20 patients), there would be 93%, 88% and 81% power to detect a 74% difference between the proportion of patients on target for SBP for an ICC of 0.05, 0.07 and 0.10, respectively, p = 0.05.

Descriptive statistics (mean, median, number of observations, standard deviation, standard error, 95% confidence intervals - minimum and maximum) of all primary and other variables will be tabulated. Given the expected clustering of patients for each physician, multilevel mixed modelling will be performed using SAS GLINMIX for categorical variables (target attainment after 12 months in the benchmarking group compared with the control group, and target attainment after 12 months compared with baseline levels) and SAS Prox MIX for continuous variables (mean percentage improvement of HbA_1c_, LDL-cholesterol and SBP after 12 months follow up).

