Centres or sites were selected on the basis of having sufficient patients with diabetes in their practice and with investigators that were motivated to fulfil the administrative procedures linked to the study. Centres or sites were randomised by a central randomisation procedure to either a benchmarking group or a control group. To ensure that country-specific treatment practices were reflected in the study population, the centres or sites involved in the management of diabetes that were recruited, consisted of general practitioner or hospital-based outpatient clinics. Recruitment for the study began initially in Belgium with a randomisation ratio of 1:1. Each centre was expected to recruit 8-12 patients; however, some centres enrolled 15-20 patients. The adapted sample size analysis showed that a power of 79% was achieved for the parameter blood pressure and a significance level of 0.05 was achieved for the parameters HbA_1c _and total cholesterol. As sufficiently high numbers of physicians were recruited in Belgium, this subsequently allowed a 3:1 randomisation ratio of benchmarked to control practices in the other countries, which was deemed more attractive to the participating physicians. All physicians involved in the study continued with the routine monitoring, treatment and counselling of their patients with T2DM. Over the course of the study, physicians in both groups received the results of modifiable outcome indicators (HbA_1c_, fasting glycaemia, total cholesterol, high-density lipoprotein [HDL]-cholesterol, LDL-cholesterol and triglycerides [TG]; determined in a central laboratory). Physicians in the benchmarking group additionally received information on the level of control of the critical quality indicators of their individual patients, anonymously compared with the results of their colleagues from the same country, and compared with target levels (Figure 2). This benchmarked feedback was provided every 4 months, corresponding to three- to four-times yearly control visits, as recommended by international guidelines [15]. The study recruitment and initiation visit was defined as Visit 1 out of the four visits.

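### The power printed for clusters of 10 (91/86/80%) does not follow from its stated inputs, and the detectable effect of 7.4 percentage points is printed as 74%

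*Protocol article*

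**What the plan says.** The Protocol article, Statistical considerations, bases the sample size on attainment of the SBP target. Both groups are expected to reach 23.2%, and benchmarking "could further improve the level of blood pressure control by 32%, i.e from 23.2 to 30.6" per cent. Three scenarios follow, each with 3000 benchmarking and 1000 control patients and ICCs of 0.05, 0.07 and 0.10:

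- 300 + 100 clusters of 10: an unpooled two-sided Z test "would give 91%, 86% and 80% power to detect a 74% difference between the proportion of patients on target for SBP".
- 200 + 67 clusters of 15: "there would be 96%, 93% and 88% power to detect a 74% difference".
- 150 + 50 clusters of 20: "there would be 93%, 88% and 81% power to detect a 74% difference".

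The level appears only with the two adapted scenarios ("for an ICC of 0.05, 0.07 and 0.10, respectively, p = 0.05").

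Study design gives a further figure: "The adapted sample size analysis showed that a power of 79% was achieved for the parameter blood pressure". The same sentence adds that "a significance level of 0.05 was achieved for the parameters" HbA1c and total cholesterol.

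**The concern.** The three scenarios share total patients, target rates and ICCs; only cluster size changes. Larger clusters carry less information per patient, so clusters of 10 should give the highest power. The article gives them the lowest at every ICC. The effect to be detected is given as 74% three times, although the rates a sentence earlier differ by 7.4 points. The 79% in Study design is described as coming from the adapted analysis, but the adapted figures in Statistical considerations run from 81% to 96%.

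These are the only figures offered for the size of the trial, and a null result would be read against them. A reader who tries to check them cannot do so.

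**Working it through.** **Inputs** (all from Statistical considerations): control 23.2%, benchmarking 30.6%; two-sided unpooled Z test; cluster counts and sizes as listed; ICC 0.05, 0.07, 0.10. Alpha 0.05 is stated for the adapted scenarios and assumed for clusters of 10. The control arm is 67 × 15 = 1005 in the 15-patient scenario and 1000 in the other two.

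**Formula.** Design effect DE = 1 + (m − 1) × ICC. SE² = DE × [0.232 × 0.768 / n(control) + 0.306 × 0.694 / n(benchmarking)]. Power = Φ(0.074 / SE − 1.96).

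**Clusters of 10.** The bracket is 0.178176/1000 + 0.212364/3000 = 0.00024896.

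| ICC | DE | SE | 0.074/SE | Power | Printed |
|---|---|---|---|---|---|
| 0.05 | 1.45 | 0.01900 | 3.895 | 97.3% | 91% |
| 0.07 | 1.63 | 0.02014 | 3.673 | 95.7% | 86% |
| 0.10 | 1.90 | 0.02175 | 3.402 | 92.5% | 80% |

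The printed values would need design effects of about 2.0, 2.4 and 2.8. Other conventions do not recover them:

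- pooled variance: 96.7/94.7/91.1%
- one-sided: 98.8/97.9/96.1%
- continuity-corrected: 97.1/95.4/92.1%
- t reference with clusters − 2 degrees of freedom: 97.3/95.6/92.4%
- both variances at the control rate: 97.9/96.4/93.6%

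**Clusters of 15 and 20**

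| m | ICC | Unpooled | Control-rate variance | Printed |
|---|---|---|---|---|
| 15 | 0.05 | 95.0% | 95.8% | 96% |
| 15 | 0.07 | 91.6% | 92.8% | 93% |
| 15 | 0.10 | 85.8% | 87.4% | 88% |
| 20 | 0.05 | 91.9% | 93.0% | 93% |
| 20 | 0.07 | 86.7% | 88.2% | 88% |
| 20 | 0.10 | 78.6% | 80.5% | 81% |

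Under the stated test the printed values are 1.0 to 2.4 points high. With 0.232 × 0.768 used for both arms, all six agree within 1 point.

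**Ordering.** At 3000 versus 1000 patients, DE rises with m, so power falls. The unpooled test gives 97, 95, 92% (ICC 0.05), 96, 92, 87% (0.07) and 92, 86, 79% (0.10; 92.5% before rounding for m = 10) for m = 10, 15, 20. The printed sequences are 91, 96, 93; 86, 93, 88; and 80, 88, 81. The step from 15 to 20 goes the right way; the step from 10 does not. No single convention applied to all three scenarios can produce that order.

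**A possible source.** With 200 + 67 clusters of 10 (2000 + 670 patients), the unpooled test gives 89.0/85.2/79.5% and the control-rate variance 90.3/86.8/81.3%, both near 91/86/80%. This is an inference from the fit; the article does not say it.

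**Effect.** 30.6 − 23.2 = 7.4 points, and 23.2 × 1.32 = 30.6, so 32% relative. A 74% relative rise would be 23.2 × 1.74 = 40.4%, with power of essentially 100% in the 10-patient scenario.

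**The 79%.** No ICC, cluster size or patient number is attached. It would fit clusters of 20 at ICC 0.10 (78.6% unpooled, where 81% is printed). Under assumed inputs it would equally fit a Belgian 1:1 stage: 1095 per arm (half of Belgium's 2190 in Table 2), m = 15 and ICC 0.07 give 79.5%.

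**The case against.** Four points can be made for the article.

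1. A reader might infer that none of the power figures is right. The documents do not support that. The 15- and 20-patient sets are in the correct order, close under the stated test, and within 1 point under another variance convention. What remains there is a small mismatch with the word unpooled.
2. A reader might take the 79% as contradicting the 81% for clusters of 20 at ICC 0.10, since 78.6% rounds to 79%. That rests on a numerical coincidence. The sentence stands between the account of Belgian 1:1 recruitment and the move to 3:1, so it may concern the Belgian stage. It is unreconciled, not shown to be wrong.
3. A reader might count it an error that every scenario is 3:1 while 2484 and 1510 patients were enrolled. Planning scenarios need not match enrolment, Study design explains the differing ratios, and the enrolled split lowers no stated power.
4. The 74% looks like a lost decimal point, and the true rates stand in the same paragraph. This limits the harm, but the effect is still misstated each time power is given.

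None of this rescues the 10-patient set. The ordering fails whatever the variance formula or sidedness, provided one convention is used throughout.

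**Conclusion.** The point holds for the 10-patient set and for the effect label. For 300 + 100 clusters of 10, the printed 91/86/80% should be 97.3/95.7/92.5%, if the cluster counts are right and alpha is 0.05 as in the adapted scenarios. The calculation assumes equal cluster sizes and the usual design effect. The 15- and 20-patient sets are slightly high under the stated test. The 74% should be 7.4 percentage points. The 79% cannot be placed among the adapted figures. A significance level is set in advance and is not something that a sample-size analysis achieves.

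It would be tempting to conclude that the trial is underpowered. The figures do not show this: the main error understates power, and the lowest corrected value in the three scenarios is 78.6%, for clusters of 20 at ICC 0.10. This is a reporting correction. It changes no patient number and no analysis.

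**What to change.** 1. Establish from the sample-size records whether the cluster counts or the powers in the 10-patient scenario are wrong. If 300 + 100 clusters stand, print about 97/96/92% (92.5% before rounding). If the powers came from about 200 + 67 clusters, correct the counts and patient totals, and recompute.
2. Restate the 15- and 20-patient sets as 95/92/86% and 92/87/79% under the unpooled test, or name the variance formula that gives the printed values.
3. Write 7.4 percentage points (32% relative) in all three places.
4. In Study design, give the ICC, cluster size, patient numbers and allocation behind the 79%, and say what was meant for HbA1c and total cholesterol; otherwise delete the sentence.
5. Optionally, add a row for the enrolled allocation. With 2484 and 1510 patients, 3994/370 = about 10.8 per site and equal clusters assumed, the same formula gives about 99/98/96%.

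The cost is a text correction. Some printed values in the 15- and 20-patient sets become 1 to 2.4 points less favourable.

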The OPTIMISE trial has several strengths. Contrary to many studies in the field of quality improvement, this study uses a monofactorial intervention allowing its potential effects to be easily studied and contextualised. It randomises at the clinic level and not at the patient level to avoid confounding effects from physicians having both intervention and control patients. Results are analysed at the patient level as this is more clinically meaningful. Importantly, the RCT design avoids any positive effect bias that may be induced by increased attention caused by participation in a study, or by selecting more motivated physicians, or by overall changes in T2DM care over the study period. A possible confounder of the study may be the frequency of determining the quality indicators, which was pre-specified in the protocol. Frequency of testing may have increased for both groups of patients in the study compared with their testing frequency prior to study initiation. This alone may have led to an improvement in target attainment in both groups. One possible limitation of the study is that LDL-cholesterol levels were estimated using Friedewald's formula, rather than being directly measured. However, this reflects real-life clinical practice. A further limitation may be the requirement to establish a history of proteinuria from patient medical records, as proteinuria may not be routinely tested for and recorded. In addition to investigating the effects of benchmarking, the OPTIMISE study offers an opportunity to obtain comparable data on the quality of primary care received by patients with T2DM in six European countries. It is difficult to obtain comparable data across different European countries due to heterogeneity in data collection. Therefore, the OPTIMISE data have the potential to offer a particularly useful resource for European healthcare providers, and help inform diabetes care policy decisions at the European level along with other initiatives such as the European Core Indicators in Diabetes project (EUCID), which aims to create a platform to collect and analyse data on health status and care delivery for diabetes in Europe [41].

In summary, although feedback with benchmarking is a promising tool for quality improvement in chronic care in general, and in diabetes care specifically, there is a striking lack of clinical evidence from controlled trials. The results from OPTIMISE may have the potential to contribute to filling this gap.

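### Centres were randomised, but the ICC and the mixed model name only physician clustering; the model should carry a random effect for the randomised centre

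*Protocol article*

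**What the plan says.** All places are in the protocol article.

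- **Unit randomised.** Study design: "Centres or sites were randomised by a central randomisation procedure to either a benchmarking group or a control group". The Discussion lists this as a strength: "It randomises at the clinic level and not at the patient level".
- **Unit receiving the intervention.** Target setting for benchmarking: "benchmarked feedback was given to each practice for both the pooled patient population at that practice, and at an individual patient level".
- **Unit behind the ICC.** Statistical considerations starts from the investigator's own way of managing patients: "it was expected that this might result in an investigator or cluster effect". An ICC of 0.05 to 0.10 for blood pressure follows.
- **Unit behind the sample size.** Study design: "Each centre was expected to recruit 8-12 patients; however, some centres enrolled 15-20 patients". Statistical considerations uses clusters of 10, then of 15 and 20 because some centres were larger. Here the cluster is in effect the centre.
- **Unit named for the analysis.** Statistical considerations: "Given the expected clustering of patients for each physician, multilevel mixed modelling will be performed", with the SAS procedures for generalised linear and linear mixed models. No random effects are listed and no centre effect is mentioned.
- **Type of centre.** Study design: they "consisted of general practitioner or hospital-based outpatient clinics". The number of participating physicians per centre is not given.

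**The concern.** In a cluster-randomised trial all patients of a randomised unit share one arm, so any variation between units enters the comparison of arms directly. The analysis has to carry that variation at the level of the randomised unit or above.

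Here that unit is the centre, while the level named for the model is the physician. If two or three physicians worked in one randomised centre, a model whose highest random effect is the physician would treat them as independent, although they share an allocation and perhaps a local way of working. The standard error of the benchmarking effect would then be too small and the false-positive rate above the nominal 5%. The primary comparison, target attainment at 12 months, is the one affected.

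**Working it through.** **1. The plan's own figure.** The stated power for 300 + 100 clusters of 10 is 91%, 86% and 80% at ICC 0.05, 0.07 and 0.10. With an unpooled two-sided Z test, 30.6% against 23.2%, and design effect 1 + 9 × ICC:

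SE = √[(1 + 9 × ICC) × (0.306 × 0.694/3000 + 0.232 × 0.768/1000)]

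At ICC 0.05, SE = 0.0190, 0.074/0.0190 = 3.89, and power = Φ(3.89 − 1.96) = 97.3%. At 0.07 and 0.10 I get 95.7% and 92.5%. The stated values are not reproduced. That is a separate matter and does not bear on this point. What matters here is that the cluster size in this calculation is patients per centre.

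**2. Inputs for the check.**
- Patients per centre: 3994/370 = 10.8 (Results).
- Correlation between patients of the same physician, ρp: 0.05 to 0.10 (Statistical considerations).
- Physicians per centre, k: not in the document; assumed 1, 2 or 3.
- Correlation between patients of different physicians in the same centre, ρc: not in the document; assumed half of ρp or equal to ρp. Equality is the extreme, with no physician variation beyond the centre.

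**3. Formulas.** With m = 10.8/k patients per physician:
- design effect in a physician-only model: Dp = 1 + (m − 1)ρp
- design effect allowing for the centre: Dc = Dp + m(k − 1)ρc
- ratio of true to modelled standard error: r = √(Dc/Dp)
- actual two-sided type I error: 2[1 − Φ(1.96/r)]

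Example with k = 2, ρp = 0.05, ρc = 0.025: Dp = 1 + 4.4 × 0.05 = 1.22; Dc = 1.22 + 5.4 × 0.025 = 1.355; r = 1.054; error 6.3%.

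**4. Every centre with k physicians** (each range is over ρp = 0.05 to 0.10).

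| k | ρc | r | Type I error |
|---|---|---|---|
| 1 | any | 1.00 | 5.0% |
| 2 or 3 | 0 | 1.00 | 5.0% |
| 2 | ρp/2 | 1.05-1.09 | 6.3-7.2% |
| 2 | ρp | 1.11-1.17 | 7.6-9.5% |
| 3 | ρp/2 | 1.08-1.13 | 6.9-8.4% |
| 3 | ρp | 1.15-1.25 | 8.8-11.8% |

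A second set of assumptions gives a similar range: k = 2 to 4, centre ICC 0.02 to 0.05, and a further physician ICC of 0.05 to 0.07. The error is then about 5.9-9.1%. At its top that set sums to 0.12, above the article's 0.10.

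**5. Only some centres with several physicians.** A rough analytic version averages the design effects over a fraction q of multi-physician centres. For q = 0.25, k = 3 and ρc = ρp = 0.10: model 0.25 × 1.26 + 0.75 × 1.98 = 1.80; true 1.98; r = 1.049; error 6.2%. For q = 0.10, k = 2 and ρc = ρp/2 the error is 5.1-5.2%.

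A simulation used 370 centres (an assumed 230/140 split), ICC 0.10, 2-3 physicians in multi-physician centres and ρc from half of ρp to ρp. It gave about 5-7% for q = 10-25%, 7-9% for q = 50% and 7-12% for q = 100%, with a simulation error of about 0.6 points.

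**The case against.** A reader might infer that the article specifies a physician-only model and that its standard error is therefore too small. The document supports neither step.

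First, the sentence on clustering gives a reason for multilevel modelling. It lists no random effects and does not exclude a centre level, and a condensed article may leave the model statement to the full plan.

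Second, nothing shows that any centre had more than one participating physician. Admitting hospital outpatient clinics makes that possible but does not establish it. The wording fits one investigator per centre equally well: physicians, practices, investigators and centres are used almost interchangeably, and 8-12 patients is a plausible load for one investigator. The sample-size clusters already follow the centre, so the design calculation does not ignore the randomised unit. Every error rate above 5% also rests on assumed values of k and ρc, and the higher ones assume that every centre has several physicians.

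All of this stands against a claim of demonstrated error inflation. It does not remove the mismatch. The unit randomised and used for sizing is the centre, the only unit named for the ICC and the model is the investigator or physician, and the document never says that they are the same. A two-level model of patients within physicians is itself multilevel, so an analyst who followed the text could fit it in good faith.

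**Conclusion.** The point holds in conditional form. The conflict between the randomised unit and the named clustering unit is on the page. Its statistical consequence needs two things that the document does not give: centres with more than one participating physician, and a positive correlation across physicians within a centre. If either is absent, a physician-level model is valid and no result changes.

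If both are present and the model stops at the physician, type I error is about 5-7% when 10-25% of centres have several physicians. When all do, it is about 6-9% or somewhat more, with about 12% at the extreme of the assumed values. The direction is neutral or anti-conservative. It is worth correcting because it concerns the primary comparison and the repair is nearly free, not because inflation has been shown.

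**What to change.** In the analysis paragraph of Statistical considerations, specify a random intercept for the randomised centre in both the GLIMMIX and MIXED models. Nest physician within centre where a centre has more than one, and base the degrees of freedom for the arm comparison on the number of centres. In the sample-size paragraph, describe the cluster and its ICC as those of the centre, which matches the cluster sizes already used there. If every centre had a single participating physician, one sentence saying so would settle the matter.

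The cost is at most one extra random term, plus a physician identifier where centres have several. Intervals may widen slightly if multi-physician centres exist; otherwise the results are unchanged.
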